## Abstract

**Background:**

Inadequate parenting is an important public health problem with possible severe and long-term consequences related to child development. We have solid theoretical and political arguments in favor of efforts enhancing the quality of the early family environment in the population at large. However, little is known about effect of universal approaches to parenting support during the transition to parenthood. This protocol describes an experimental evaluation of group based parenting support, the Family Startup Program (FSP), currently implemented large scale in Denmark.

**Methods/design:**

Participants will be approximately 2500 pregnant women and partners. Inclusion criteria are parental age above 18 and the mother expecting first child. Families are recruited when attending routine pregnancy scans provided as a part of the publicly available prenatal care program at Aarhus University Hospital, Skejby. Families are randomized within four geographically defined strata to one of two conditions a) participation in FSP or b) Treatment As Usual (TAU). FSP aims to prepare new families for their roles as parents and enhance parental access to informal sources of support, i.e. social network and community resources. The program consists of twelve group sessions, with nine families in each group, continuing from pregnancy until the child is 15 months old. TAU is the publicly available pre- and postnatal care available to families in both conditions. Analyses will employ survey data, administrative data from health visitors, and administrative register based data from Statistics Denmark. All data sources will be linked via the unique Danish Civil Registration Register (CPR) identifier. Data will be obtained at four time points, during pregnancy, when the child is nine months, 18 months and seven years. The primary study outcome is measured by the Parenting Sense of Competence scale (PSOC) J Clin Child Psychol 18:167-75, 1989. Other outcomes include parenting and couple relationship quality, utility of primary sector service and child physical health, socio-emotional and cognitive development.

**Discussion:**

The protocol describes an ambitious experimental evaluation of a universal group-based parenting support program; an evaluation that has not yet been made either in Denmark or internationally.

**Trial registration:**

ClinicalTrials.gov ID: NCT02294968. Registered November 14 2014.

## Background

### Specific background and explanation of rationale

Inadequate parenting is a significant public health problem and may potentially have life-long consequences for the affected children’s physical and mental health, educational attainment, labor market success, and family formation (see for example [1,2]). Inadequate parenting spans from childrearing practices characterized by lack of resources, knowledge, skills and confidence to severe forms of physical and emotional ill-treatment, sexual abuse, neglect, and exploitation. Most recent Danish estimates range from one in five families being at risk of inadequate parenting resources [3] to 0.05 per thousand children being at risk of terminal child maltreatment [4].

There are solid arguments for strengthening parenting support as early as possible. As a result of their dependency, vulnerability and relative social invisibility, infants are more exposed to risks related to inadequate parenting than older children. Infant cases are also the least likely to come to the attention of anyone outside the family that can monitor their care and safety [1]. Furthermore, research into early brain development indicates that the brain’s development can be physiologically altered by severe stress imposed by inadequate parenting during a child’s early years [5]. Insecure attachment and poor stimulation can reduce cognitive and emotional functioning and slow physical growth can increase the risk of illness in adulthood [6].

There are also sound economic arguments for early investments. Recently, Heckman and co-authors have emphasized the importance of investing early in particularly vulnerable children. Cunha and Heckman, for example, show theoretically that early investments not only have a large potential pay-off, they are also efficient in the sense that there does not exist an equity-efficiency trade-off, which is the case for later investments [7]. The reasons are that, in their model, skills acquired in one period persist into future periods and that skills produced at one stage raise the productivity of investment at subsequent stages. Importantly, skills are multidimensional and are likely to complement each other.

The transition to parenthood provides optimal opportunities for reaching families. Couples expecting or having their first child are often eager to prepare for their roles as parents [8] and in Denmark, high rates of attendance are observed in preventive or educational programs offered to all couples during transition to parenthood [9].

To date, some prevention research has shown promise in enhancing parenting practices during the transition to parenthood, but most of these studies have focused on high-intensity service delivery (e.g. home visits) to specific subsets of abusive parents or disadvantaged families (e.g. [10-12]). This paucity of evidence regarding large scale primary prevention programs raises concerns that scarce resources may be wasted through investment in well-intentioned initiatives whose effectiveness may never be proven.

### Effects of universal parenting programs during the transition to parenthood

Universal approaches to parenting support have as their general aim to enhance the quality of the early family environment in the population at large (as opposed to targeting a specific problem in identified cases of families and children with special needs). For example, in a randomized trial of prenatal parent education, all nulliparous women allocated to routine care were included, and effects related to pregnancy worry, the birth process, and prenatal confidence in breastfeeding were found [13-15]. To the authors’ knowledge, no experimental design study was previously conducted on large scale implementation of universal group based parenting support with both pre- and postnatal program elements. The existing experimental studies are small scale or university-based and deliver infant care education primarily to mothers in group or class formats (for reviews see [8,16]). Data from these studies provide for some optimism with regard to the ability of infant care education to produce small to moderate effect size improvements on maternal adjustment and postpartum parenting skills [8,17]. However, the literature is sparse when it comes to how the effects from university settings generalize, when programs are implemented at the population level and what the long term effects and consequences for child outcome may be. Also, studies including fathers are few and with mixed conclusions. This may be particular surprising given the amount of research that point toward a direct link between fathers’ early involvement and the child’s social and cognitive development (for review see [16]).

When implementing the “Building Strong Families” parenting program in the US, fathers and family stability were the primary target, yet no positive effects were found on relationship satisfaction, marriage or father involvement [18,19]. In line with this, Trillingsgaard, Baucom, Heyman & Elklit found no effects of the couple-focused intervention “PREP” when offered to Danish men and women during pregnancy [20]. Halford, Petch, & Creedy compared effects of a) a maternal education program and b) a couple-focused education program “Couple Care”, and found effects on mother reports only [21]. Among more successful programs, Doherty, Erickson, & LaRossa examined an 8-session group based and couple-focused intervention and found positive effects on fathers’ skills in interacting with their babies and their involvement with child on work days but not home days [22]. Also, a study conducted by Schulz, Cowan & Cowan found that 24 weekly group meetings involving fathers in discussions of parenthood and the couple relationship helped both partners sustain relationship adjustment for up to five years after the birth [23].

In summary, the existing literature suggests that universal group-based parenting support programs may have at least short term positive effects on parenting outcome, when programs are conducted in controlled settings and are mother-child focused. When it comes to extending the scope and aim of these types of interventions, we have mostly theoretical and political arguments. The effects to be gained from intervening at the population level, also targeting fathers, and examining longer term child outcome are largely unknown.

### Rational of the Family Startup Program

The FSP is a structured format for implementing pre- and postnatal parenting support groups that prepare new families for their roles as parents and enhance parents’ access to information sources of support, i.e. social network and professionals representing community resources (for manual, see [24]). The program content includes handling family finance, choice of paternity leave, couple communication, breastfeeding, network formation, ensuring dental health, sensitivity toward child signals, child rearing discipline, help-seeking behavior, home safety, and more. Thus the FSP has not one but a wide range of possible learning outcomes most of which relate to a central rational of empowering parents by enhancing their sense of competence and lowering parental stress across the transition to parenthood. A second formulated rational behind the program is that strengthening father involvement, social network formation and access to family services will serve to enhance family relationships, including parenting, coparenting and couple relationship quality [24]. Through participation in FSP families receive a long term connection with a health visitor in the community and are introduced to a broad range of community services. This can be expected to benefit optimal health service utility and ease access to resources for families and children with need of additional support. Improved child outcome is the ultimate goal. No scientific evaluation of program effects of the FSP on child or family outcome was previously conducted.

### Specific objectives and hypotheses

The aims of this study is to determine whether a group-based parent support program can lead to:Early improved parental sense of competence (primary outcome)Continued improvement in parental sense of competence (secondary outcomes)Reduced parental stress (secondary outcomes)Improved quality in early family relationships, that is improved quality of parenting, coparenting and couple relationship quality (secondary outcomes)Improved efficiency in service delivery, that is increasing surveillance of families at risk, and enhancing families’ utility of community resources, social network and family services (tertiary outcomes)Improved child outcomes including better physical health and improved socio-emotional and cognitive development (tertiary outcomes)Heterogeneity of effects across family type with disadvantaged families and families met with a more mature program implementation gaining more from participation (tertiary outcomes).

## Methods

### Trial design

The study is an individually superior randomized controlled trial with two parallel arms. The experimental group is offered FSP and the control group TAU.

### Participants

#### Inclusion criteria

Parents, mothers as well as their partners, expecting their first child in the municipality of Aarhus are eligible for the study. Mothers are included if interested regardless of the fathers’ decline. Biological fathers, registered partners, as well as non-registered partners are eligible.

### Exclusion criteria

Parents are excluded from the study if they are under the age of 18 years, not capable of managing own legal affairs, are found by their general practitioner to be in need of drug or alcohol abuse treatment, if they choose not to accept any routine pregnancy scans, or were not willing to provide signed consent. These exclusion criteria are chosen to secure that study participants are legally responsible and that we are able to recruit them via the Department of Obstetrics and Gynaecology in connection with the standard pregnancy scans.

The father or partner is not included if the mother declines participation. The mother can choose to attend the FSP with a friend (i.e. a sister, friend or neighbor) but friends are not eligible for the study. Finally, individuals are excluded if they do not have sufficient Danish skills. The rationale for this is the group nature of the program.

### Setting

This study is conducted in the municipality of Aarhus, Central Region Denmark. The inclusion began on November 24, 2014. Parents will be recruited through Aarhus University Hospital, Skejby, Department of Obstetrics and Gynecology. All pregnant mothers who fulfill the inclusion criteria and are referred from the general practitioner to receive pregnancy care at the hospital will be informed about the study. Information about the study and recruitment will take place at the Ultrasound Department at Aarhus University Hospital in week 12 or 19 of gestational age.

### Interventions

During the project period, the experimental group will receive the FSP and the existing publicly available pre- and postnatal care services.

### The Family Startup Program

FSP is a group-based manualized program for implementing pre- and postnatal parenting support that prepares new families for their roles as parents. The approach is inspired by community work conducted in the town of Leksand, Sweden [25]. The Danish manual details the content for each session, both in terms of themes, in terms of time (down to five minute intervals), and in terms of teaching material. The manual is copy-righted but for purposes of replication can be required from the Department of Children and Youth in Aarhus Municipality (“Mødeguiden”; [24]).

The program has an explicit focus on the enhancement of parents’ social network. Parents assigned to the FSP are offered 12 group (ideally consisting of 9 families) meetings whereof 2 meetings take place before the birth of the child, starting around week 28 of the pregnancy, and 10 meetings are scheduled after the birth of the child. The program lasts until the child is around 15 months old. Meetings are held from 4.30-6.30 pm to minimize interference with families’ working lives.

### Meeting structure, didactics, and teaching material

The program is delivered in two-hour face-to-face sessions with a health visitor as the permanent group leader. Participants are introduced to a broad range of community resources by means of oral presentations from e.g. financial advisers, legal advisers, psychologists, physiotherapists, and family counselors providing them with information about the specific theme of the session. The timing of sessions and their content are shown in Table 1.

**Table 1 Tab1:** **Timing of session and content in Family Startup**

**Meeting**	**When?**	**The topic of the day/presentations**	**Teacher(s)**
1	Week 28	Welcome and presentation of the program	Heath visitor
		Finances and changes in the budget of the family Networking	Financial adviser
		What does an infant need	Nurse
2	Week 32	How to ensure and insure each other?	Legal adviser
		Legal paternity- what does it mean?	Health visitor
THE BIRTH OF THE CHILD			
3	Child 1 month	Relationships, communication, and sleep	Marte Meo therapist
		The everyday life with an infant	Health visitor
4	Child 2 months	Motor development in infants	Physiotherapist
		The infant’s basic needs	Health visitors
		Psychological reaction after the birth	Health visitor
5	Child 3 months	Family dynamics and interaction	Psychologist and health visitor
		Help and support- what are the possibilities?	
6	Child 4 months	Food and meals	Health visitor
		Medical check-up of the child	
7	Child 5 months	Preventing accidents	
		When your child is sick	Health visitor
8	Child 6 months	Language development	Language counsellor
		Child development	Health visitor
9	Child 7 months	The labor market and daycare enrolment	Pedagogue
		Sleep during day and night- how to get better sleep	Health visitor
10	Child 8 months	The personality of your child and independence	Health visitor
		The child’s first tooth	Dentist
11	Child 10 months	Family dynamics	Family counselor/pedagogue
		The everyday life with your child	Health visitor
12	Child 15 months	Upbringing: the everyday life and challenges in the family Resilience	Health visitor
		Goodbye	

The group leader facilitates discussion and arranges exercises before and after the oral presentations. The fixed structure of the meetings is as follows:Follow-up on last meetingPresentation of first theme of the dayDiscussion and debate based on presentationSummary of discussionBreak and refreshments/dinnerPresentation of second theme of the dayDiscussion and debate based on presentationClosing words, next meeting’s themes, evaluation.

The teaching style is dialogic and participants are directly involved through discussion, both in plenary sessions and in smaller groups (mixed gender, single gender, couples on their own). The manual includes PowerPoint presentations, video material, exercise sheets, evaluation sheets, and teaching instructions.

### Adherence

A set of procedures will ensure that the program is delivered to meet the standardized version of FSP. As described, program fidelity is supported by the detailed manual (“Mødeguiden”, Guideline for meetings in Danish; [24]). All health visitors, who will be group leaders, participated in a 3-day workshop on facilitating family group meetings prior to the study. A program manager (health visitor) is employed full time and will visit groups during sessions to facilitate and ensure quality of delivery. A brief measure of satisfaction with program will be obtained from all parents at three random sessions during the course of the program. Further, the group leader fills out a checklist at the end of each session, monitoring whether or not the main content was covered.

### Treatment as usual

The existing publicly available pre- and postnatal care service includes two group-based sessions of birth preparation, routine pregnancy visits to the general practitioner and midwife, and postnatal home visits by nurse. Specific pre- and postnatal care services target families with a certain profile (history of loss, history of depression, parents expecting twins or young mothers). None of the existing services will be affected by the addition of the FSP and Randomization. *All* families will be offered these existing services, regardless of their treatment assignment.

### Measures including outcomes

Our analyses will employ three main data sources with information about parents and children: survey type information, administrative data from health visitors, and administrative register based data maintained by Statistics Denmark. All data sources will be linked through the unique Danish Civil Registration Register (CPR) number and data will only be accessed in anonymous form.

Survey data will be collected by an email sent to both partners in the family with personal login to a web-based survey using the online survey solution *SurveyXact*. Two reminders are sent by email. Participants can choose to answer questionnaires through the telephone call if preferred. Survey data will be obtained at four time points, during pregnancy, when the child is nine months, 18 months and seven years. No monetary incentives are used to motivate participation. Lottery prizes with a value of maximum DKK 3,000 per prize will be drawn from the pool of project participants, who fill in the questionnaire.

### Background information and control variables

Information about parent age, gender, marital status and relationship stability, educational background, employment status, previous psychiatric/therapeutic treatment, smoking, place of birth, siblings, and receipt of welfare will be collected through survey single items during pregnancy or obtained through registers. Financial strain is measure with a 3-item scale [26], and social desirability is measured with 10 items adapted from the 31 items version of the Social Desirability Scale [27].

Background information on eligible individuals who do not enrol in the study is available from register-based data. In addition to these data we will ask decliners about their language skills, educational level and reason for decline.

### Secondary study outcomes

*PSOC* measured at 18 months and seven years.

*Parenting stress* is measured with the Parenting Stress Scale [32] at nine months, 18 months and seven years.

*Parenting Quality* is measured at nine and 18 months with the Parenting Scale [33] and we intend to use the HOME inventory as nurse administrative data [34] at nine months. At nine and 18 months, a measure of father-involvement developed for the study and a single item on breastfeeding duration will be included.

*Quality of the Couple Relationship* is measured with the Couple Satisfaction Index [35] during pregnancy at nine months, at 18 months and at six years, and the Coparenting Relationship Scale [36] at nine months and 18 month, and divorce rate at seven years.

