### Statistical methods

Reporting of results will follow the guideline of the CONSORT- statement. Statistical analysis will be intention to treat. The level of significance will be 0.05. The primary endpoint is PSOC at the nine month follow-up. The intention-to-treat analysis will compare FSP with TAU using both simple two-sample t-tests, non-parametric rank based tests (Wilcoxon), and linear regressions (ANCOVA) that control for pre-randomization variables (parents’ age, marital status, educational background, employment status, previous psychiatric/therapeutic treatment, smoking, place of birth, own number of siblings, receipt of welfare, financial strain, and social desirability). This latter analysis will cluster errors at the FSP group level. Except for the divorce rate at the seven year follow-up, which is binary in nature, all statistical analyses of effects on secondary outcomes will follow our strategy for the primary outcome. For divorce rate, we will use simple two-sample t-tests as well as a logistic regression that control for pre-randomization variables. Similar principles will be applied to the analysis of tertiary outcomes.

In addition to intention-to-treat analysis, we will also perform contamination adjusted intention-to-treat analysis, which complements the intention-to-treat approach by producing a better estimate of the benefits and harms of receiving a treatment. This method uses the statistical technique of instrumental variable analysis to address contamination [41-46].

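### The only couple break-up outcome is divorce, which enrolled couples who never marry cannot experience, so an effect on couple stability would be diluted

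*Protocol article*

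**What the plan says.** The Secondary study outcomes section lists, under quality of the couple relationship, two questionnaires (the Couple Satisfaction Index and the Coparenting Relationship Scale) and "divorce rate at seven years". No other outcome records whether the parents are still together.

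Statistical methods treats this outcome separately ("Except for the divorce rate at the seven year follow-up, which is binary in nature") and states the tests: "For divorce rate, we will use simple two-sample t-tests as well as a logistic regression that control for pre-randomization variables". The general rule in the same section is "Statistical analysis will be intention to treat". No denominator is given for divorce.

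Marriage is not an entry condition. Inclusion criteria states "Biological fathers, registered partners, as well as non-registered partners are eligible", and also "Mothers are included if interested regardless of the fathers’ decline". The background data include "Information about parent age, gender, marital status and relationship stability, educational background, employment status". Marital status is then an adjustment covariate, so a mix of married and unmarried couples is expected. Relationship stability appears only as a baseline item and a subgroup factor.

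**The concern.** The aim is better couple relationship quality across the enrolled families, but the event chosen to represent break-up is open only to those who are or become married. What happens to the others depends on the denominator:

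- **All randomized families.** An unmarried couple that separates is coded the same as a couple that stays together.
- **Couples ever married by year seven.** Unmarried couples drop out, and the set is selected on a status that can change after randomization.
- **Couples married at randomization.** The comparison is fair, because the set is fixed before treatment, but it is silent on every couple that was unmarried then.

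No choice of denominator makes divorce capture the break-ups of unmarried couples. Adjusting for baseline marital status does not recover them either. At stake is the power and meaning of the trial's one planned test of whether families stay together.

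**Working it through.** **The plan's own figure.** The Sample size section gives about 230 groups, or 2,070 families, for d = 0.20, power 0.80, significance level 0.05 (taken as two-sided), groups of nine and 20% of variance between groups. Ignoring groups, 393 per arm are needed, 786 in all. The design effect is 1 + (9 − 1) × 0.20 = 2.6, and 786 × 2.6 = 2,044 families, or 227 groups. The stated figure reproduces. It was not derived for divorce, for which the documents give no calculation.

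**Inputs for the illustration.** From the documents: 2,070 / 2 = 1,035 families per arm. Assumed, because the documents give no rates: separation by seven years 25% in one arm and 20% in the other; 40% to 70% of couples married; the same break-up risk in married and unmarried couples; no clustering.

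**Formula.** Power = Φ(|p1 − p2| / SE − 1.96), with SE = √[(p1(1 − p1) + p2(1 − p2)) / n]. With all families as denominator, divorce rate = married share × separation rate.

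| What counts | p1 | p2 | SE | Power |
|---|---|---|---|---|
| Every separation | 0.250 | 0.200 | 0.0183 | 0.78 |
| Divorce, 40% married | 0.100 | 0.080 | 0.0126 | 0.36 |
| Divorce, 50% married | 0.125 | 0.100 | 0.0139 | 0.44 |
| Divorce, 60% married | 0.150 | 0.120 | 0.0150 | 0.52 |
| Divorce, 70% married | 0.175 | 0.140 | 0.0160 | 0.59 |

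**Sensitivity to n.** The recruitment target with the planned dropout leaves 2,520 × 0.75 / 2 = 945 per arm at nine months. Power is then 0.74 for all separations and 0.33 to 0.55 for divorce over the same married shares.

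**Restricting to couples married at randomization.** Rates stay at 25% against 20%, but n per arm falls to between 1,035 × 0.40 = 414 and 1,035 × 0.70 = 724.5. Power is 0.41 to 0.63, so the loss remains under the one denominator that gives a fair comparison.

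**Sensitivity to equal risk.** Suppose unmarried couples separate more often (assumed 30% against 15%). With 50% married, all separations are 0.50 × 0.15 + 0.50 × 0.30 = 0.225 and divorces 0.50 × 0.15 = 0.075, so divorce captures 0.075 / 0.225 = 33% of break-ups. With 30% and 70% married it captures 18% and 54%.

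**Conditional part: an effect on marriage.** With all families as denominator and 25% separation in both arms, a rise in marriage from 50% to 55% moves divorce from 0.25 × 0.50 = 12.5% to 0.25 × 0.55 = 13.75%, with no change in stability. At 1,035 per arm SE = 0.0148, and the chance of a significant difference is Φ(0.0125 / 0.0148 − 1.96) = 0.13, against a nominal 0.05. The marriage shift is purely hypothetical. Among couples married at randomization it has no effect.

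**The case against.** **The term is undefined.** A condensed article may leave the operational definition of divorce, its source and its denominator to a fuller document. That stands for the denominator. It does not rescue the named event: read in its ordinary sense, divorce cannot happen to part of the enrolled population. If separation was meant, the wording should say so.

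**A reader might infer that the programme will distort the divorce comparison by changing marriage, or that the result could look like harm.** The documents do not support this. The only hook is a topic in the legal adviser's prenatal session, "How to ensure and insure each other". Nothing says the programme encourages marriage or is expected to change it, and the described program content does not mention it. Even the assumed five-point shift gives a significant result only about 13% of the time.

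**A reader might also infer that no denominator is free of bias.** That goes too far. Marital status is recorded before randomization, and couples married then form a fair comparison. The cost is coverage and power.

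**The magnitudes are assumed.** This stands. Break-up rates, effect and married share are not in the documents; 1,035 is the requirement before the dropout allowance; clustering is ignored. If register data cover non-responders, n could approach 2,520 / 2 = 1,260 per arm. The direction is secure, the figures are not.

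**Other measures cover the construct.** The two questionnaires do not depend on marriage, so relationship quality in unmarried couples is not unmeasured. They do not count break-ups.

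**Divorce may be the cleaner record.** If taken from registers, it would avoid survey attrition and unblinded self-report. That is a genuine trade-off and a reason to keep divorce as a supporting outcome.

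**Conclusion.** The concern holds for the missed break-ups. Non-registered partners are enrolled, divorce is the only dissolution outcome, and followed as written the separations of couples who never marry are non-events or excluded. This follows from the text and needs no assumed rates. The size does: on the illustrative rates above, power falls from about 0.78 to about 0.36 to 0.59, or to 0.41 to 0.63 if the analysis is restricted to couples married at randomization.

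Distortion through marriage is a conditional remark only. It would arise with all families or couples ever married as denominator, and only if the programme changed marriage.

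The point concerns one secondary outcome at seven years. PSOC at nine months and the sample size are untouched. It should be corrected, but it does not threaten the trial's main conclusion.

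**What to change.** Define the endpoint as parental separation by seven years, meaning that the two parents are no longer a couple or no longer live together, among all couples together at randomization. This includes unmarried couples and couples whose partner did not enrol. Take it from the seven-year survey, and from the linked registers where they record it. Keep the planned t-test and logistic regression. Report legal divorce as a supporting outcome among couples married at baseline. Settle the definition and denominator before any seven-year data are examined.

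The cost is a change of outcome wording and one derived variable, since a seven-year survey and register follow-up to age seven are already planned. There are three downsides. Separation is less sharply defined than a legal divorce. The survey part is exposed to attrition and to self-report by parents who know their allocation. The documents do not confirm that the registers record separation of unmarried couples, so this should be checked first; if they do not, the survey carries that part, and missing answers need a stated handling rule.
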